#### Participant timeline {13}

Screening will take place between day 90 and day 1 prior to surgery (Figs. 2 and 3). Follow-up will take place at day 7 or discharge (whichever comes first), day 30, and day 90.

**Fig. 2 Fig2:**
[figure not shown]
Spirit figure: schedule of enrolment, interventions, and assessments

**Fig. 3 Fig3:**
[figure not shown]
Study scheme

During hospitalization, the patient will be monitored daily for clinical signs of infection and CSF leakage or swelling at the surgical wound. All patients will undergo an MRI on day 90.

#### Sample size {14}

“Success” was defined as absence of the composite endpoint. The success rate of the investigational product was set similar to that of the control devices combined. The combined success rate of the control devices was determined at 91%, based upon a comparative study of the two devices [6]. The non-inferiority margin was set at 10%, this was accordance with the design used by the control devices [6] and believed to be clinically acceptable. The power of the study is 80%, with a one-sided significance level of 5%. The expected rate of attrition is 10%. Under these assumptions, a total of 228 patients are required, 114 per arm.

#### Recruitment {15}

Prior to the start of the trial, estimations of recruitment numbers were provided by all participating sites. Recruitment is currently ongoing. Due to the impact of the covid-19 crisis, the recruitment time has been extended to 12 months.

### Assignment of interventions: allocation

#### Sequence generation {16a}

The randomization schedule will be generated using an Internet-based computerized randomization program within the research management platform (RMP) and electronic data capturing system Staicy v2.33 (IQVIA MedTech, Danbury, USA). The RMP is fully validated and 21 CFR part 11 (and EU Annex 11) compliant. It is developed under an ISO27001 certified quality management system.

Patients will be stratified by study site and type of cranial surgery (craniotomy or craniectomy) in blocks of 4 and randomized (1:1) at the start of surgery.

#### Concealment mechanism {16b}

Concealment of the randomization scheme is ensured by use of the RMP which shows the user the assigned randomization per individual patient for their site only.

The assigned device will be stored in a non-transparent box directly after randomization.

#### Implementation {16c}

Randomization is performed by trained personnel other than the operating surgeon by logging into the RMP to perform randomization for each individual patient at the time.

### Assignment of interventions: blinding

#### Who will be blinded {17a}

The surgeon is blinded for group allocation until finalization of the primary closure of the dura, by concealing the allocated device in a non-transparent box.

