### Additional consent provisions for collection and use of participant data and biological specimens {26b}

Participants will be asked to consent or not to the use of their data for other research related to the investigational device, to be contacted for future studies and to share video/photographs of the surgery with the sponsor of the study.

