#### Intervention description {11a}

The patient is electronically randomized for LIQOSEAL or control device on the day of surgery by trained personnel other than the operating surgeon.The assigned dural sealant is taken out of the freezer/storage and placed in a non-transparent box.First PEEP test (for safety).Dura mater is closed with the standard method of suturing.Hemostasis should be achieved.The dura mater surface is rinsed from particles with physiological saline and kept moist.Second PEEP test (CSF leakage confirmed).Surgeon is unblinded and the dural sealant is applied.For LIQOSEAL: the dry patch is cut into the required size and positioned with the white side against the sutured area of the dura mater and compressed for 2 min with a moist gauze.For Duraseal and Adherus: the hydrogels are applied aiming at the sutured area of the dura mater, holding the device 2–4 cm away, until a thin coating (1–2 mm) is formed.9.Third PEEP test (2 min after device implantation).10.Standard closure of cranial defect and soft tissue will then be undertaken per surgeon standard.

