#### Outcomes {12}

##### Primary endpoint

The primary endpoint is a composite endpoint defined as the occurrence of any of the following within 90 days of surgery:

Wound infection defined in accordance with the Centers for Disease Control and Prevention guidelines as deep incisional (cat II) or organ or space infection (cat III) [8].Intraoperative CSF leakage after device application at a positive end expiratory pressure (PEEP) of 20 cm H_2_O.Percutaneous CSF leakage confirmed by β-2 transferrin test.Pseudomeningocele requiring puncture, external lumbar drainage or surgical re-intervention.Pseudomeningocele >20 cc as confirmed on MRI.

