#### Procedure for unblinding if needed {17b}

The surgeon is unblinded after finalization of the primary closure of the dura, to apply the allocated device.

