##### Intraoperative data

The device used and its size, LOT number, size of trepanation, any use of autologous material, and type of suture are recorded.

To determine the intraoperative CSF leak before and after the application of the device, the PEEP will be increased to 20 cmH2O for 20 s. First, this test will be performed before closure of the dura to determine safety for the postoperative intracranial field (control of hemorrhage, swelling or other potential adverse effects). Upon completion of the primary sutured dural closure and before the application of the sealant, the closure of the dura will be evaluated for CSF leakage by repeating the test. The patient is excluded if there is no leakage at PEEP of 20 cmH2O for 20 s. Two minutes after application of the device, the test will be performed for a third time to evaluate CSF leakage. All 3 PEEP elevations and application of the device will be recorded on video. A photograph will be taken before and after device application.

After the procedure, end users (surgeons, scrub nurses) will be invited to complete several closed-end questions regarding their user experience with LIQOSEAL.

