##### Postoperative data

During the hospitalization, the subject will be monitored daily for clinical signs of infection. The surgical wound will be inspected daily starting 24 h after surgery. Blood analysis and a wound culture will be performed if there are clinical signs of infection. In case of CSF leakage from the incision, a β-2 transferrin test will be performed. Data will be collected every 24 h from 24 h after surgery until discharge or day 7 (whichever comes first).

The clinical data to be collected on the e-CRF includes the following: body temperature.

In case of signs of infection, the following data will be collected as well: C-reactive protein (CRP), leucocytes, and culture of wound.

The signs of infection will be classified to the Centers for Disease Control and Prevention (CDC) standard of Surgical Site Infection (SSI) and recorded in the e-CRF.

All subjects will undergo an MRI on day 90. The MRI will be performed to collect data on the presence and amount of pseudomeningocele (any subcutaneous fluid on T2) as well as the long-term thickness of dura mater and investigational device.

Independent radiologists will analyze the MRIs of all subjects for the outcome measurements. Each MRI will be evaluated by 3 independent radiologists, whereas the analysis then will be based on minimally 2 out of 3 evaluations (whom are in consensus).

Postoperative assessments are not blinded.

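### Postoperative assessment is declared unblinded, although the infection class, the leak check that triggers β-2 transferrin testing and the MRI reading could be masked to the device

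*Protocol article*

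**What the plan says.** All references are to the protocol article.

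- **Who will be blinded {17a}:** "The surgeon is blinded for group allocation until finalization of the primary closure of the dura". No one else is listed.
- **Procedure for unblinding {17b}:** "The surgeon is unblinded after finalization of the primary closure of the dura, to apply the allocated device". Intervention description {11a} gives the same order ("Surgeon is unblinded and the dural sealant is applied") and places the third PEEP test two minutes after implantation.
- **Postoperative data, under {18a}:** "Postoperative assessments are not blinded". The sentence comes directly after the paragraph on MRI reading. That paragraph provides three independent radiologists, with at least two in agreement, but does not say whether they know the allocation. The same section describes daily inpatient wound inspection, CDC classification when there are signs of infection, and a β-2 transferrin test when CSF leaks from the incision.
- **Primary endpoint, under Outcomes {12}:** the composite has five components: deep or organ/space infection by CDC category, intraoperative leak after device application, transferrin-confirmed percutaneous leak, "Pseudomeningocele requiring puncture, external lumbar drainage or surgical re-intervention", and pseudomeningocele above 20 cc on MRI.
- **Intraoperative data, under {18a}:** "All 3 PEEP elevations and application of the device will be recorded on video". Under {26b}, participants may agree or decline to "share video/photographs of the surgery with the sponsor of the study".

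**The concern.** In a two-device comparison the surgeon has to learn the allocation at application, so some unmasking is unavoidable. The article goes further and declares all postoperative assessment unblinded, without separating what cannot be masked from what can. Wound checks, infection classification and imaging are done days to months after surgery. They can be done by people who were not in theatre and have no need to know the device.

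At stake is the credibility of a non-inferiority conclusion that rests on few events. At the planned 9% failure rate, about 9 failures per arm are expected (0.09 × 103 = 9.3). Small differences between arms in how readily a leak is suspected or an infection is graded deep could therefore affect the result. The plan controls neither direction.

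**Working it through.** **1. Which components could be masked**

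| Component | Judged by or when | Knows device, on the text | Masking feasible? |
|---|---|---|---|
| Intraoperative leak, third PEEP test | In theatre, after application | Yes | No for the surgeon |
| Infection, CDC category II or III | Postoperative | Not blinded | Yes |
| Percutaneous leak | Observed leak, then laboratory test | Trigger not blinded; result objective | Yes, for the trigger |
| Pseudomeningocele needing intervention | Treating team's decision | Not blinded | No for the surgeon |
| Pseudomeningocele > 20 cc | Three radiologists, day 90 | Independent, not stated to be masked | Yes, for the allocation |

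Three components have an input that can be masked. Two depend on the surgeon and cannot be.

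**2. The plan's own sample size**

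Inputs from Sample size {14}: success 91% in both arms, margin 10 points, one-sided 5%, power 80%, attrition 10%.

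n = (1.645 + 0.842)² × 2 × 0.91 × 0.09 / 0.10² = 101.3, so 102 per arm. 102 / 0.9 = 113.3, so 114 per arm and 228 in total. The stated figure reproduces, and nothing in this point changes it. Evaluable patients: 114 × 0.9 = 102.6, about 103 per arm.

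**3. How close the decision can be**

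One-sided 95% Wald upper bound for the difference in failure rates, 103 per arm, 9 control failures:

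d + 1.645 × √[p₁(1−p₁)/103 + p₀(1−p₀)/103]

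- 13 LIQOSEAL failures: 0.0388 + 1.645 × 0.0430 = 0.1095, above the margin.
- 12 LIQOSEAL failures: 0.0291 + 1.645 × 0.0421 = 0.0984, below the margin.

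This shows sensitivity near the threshold. It is not evidence of bias.

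**4. Illustration of differential under-calling**

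Assumptions: true success exactly at the margin (81% vs 91%), 103 per arm, and a fraction f of investigational-arm events not called. The article gives no value for f. Observed success is pₜ = 1 − 0.19(1 − f), and the chance of declaring non-inferiority is Φ[(0.10 + pₜ − 0.91)/SE − 1.645].

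| f | Events not called (f × 0.19 × 103) | pₜ | Normal approximation | Exact binomial, Wald test |
|---|---|---|---|---|
| 0 | 0 | 0.8100 | 5.0% | 5.3% |
| 0.05 | 1.0 | 0.8195 | 7.4% | 7.9% |
| 0.10 | 2.0 | 0.8290 | 10.8% | 11.4% |
| 0.20 | 3.9 | 0.8480 | 21.0% | 21.8% |

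Here f applies to the whole composite. Masking the three feasible inputs would remove only the part of f that arises in them. Over-calling in the investigational arm would move the figures the other way and cost power.

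**The case against.** The strongest reply is that this is a disclosed and largely forced design choice. A patch and a sprayed hydrogel cannot be hidden from the surgeon applying them, and blinding is kept up to the last feasible point, so dural closure and the second PEEP test (which decides eligibility) are protected. Percutaneous leak needs a laboratory result, infection follows CDC criteria, MRI is read by three people, and {23} requires full verification of how the main endpoints are recorded. All of this stands. It limits the concern to what could be masked and is not. It does not explain why infection classification and imaging should be open.

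Four stronger readings are tempting, and the documents do not support them.

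- **That patients know their device.** {17a} does not list them as blinded, but nothing says they are told. No listed endpoint is reported by the patient, so this is a minor route to bias.
- **That every component except MRI volume is a matter of judgement.** The transferrin result is objective; only its trigger is open. Nor is MRI clearly protected: its readers are called independent, not masked.
- **That one unblinded call decides the trial, or that bias favours LIQOSEAL.** Any binary test near its threshold turns on one event, masked or not, and no direction of bias is established.
- **That the PEEP video will go unused.** The article describes no use, but it is a condensed text and the full protocol is unpublished. Review of the footage would not be masked either, because it shows the device.

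**Conclusion.** The point holds in limited form. The article states outright that postoperative assessment is unblinded, and for three inputs to the primary endpoint (CDC class, suspicion of wound leak, MRI reading) masking is feasible. For MRI the finding rests on the text as written: the readers may in practice be masked, but the article does not say so and its closing sentence reads the other way.

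The size cannot be fixed from the documents. Under the assumptions shown, failing to call one to four investigational-arm events (f from 0.05 to 0.20) raises the false non-inferiority rate from 5.0% to between 7.4% and 21.0%. This is a range of what could happen, not an estimate. The third PEEP test and the decision to intervene remain unmasked whatever is done. The sample size is unaffected. This is an inexpensive improvement to the design, not a flaw that invalidates it.

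**What to change.** Replace the sentence in Postoperative data and extend {17a} so that:

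1. Participants are not told their device until the day-90 visit is complete.
2. An existing site team member who was not in theatre and does not know the allocation does the day-30 and day-90 wound checks and assigns the CDC class, and does the inpatient checks where feasible.
3. The three radiologists already planned receive the MRIs without the allocation. Because the scans are also used to measure device thickness, the images may sometimes reveal the device; the text should acknowledge this.
4. The article states plainly that the third PEEP test and the intervention component remain unmasked.
5. The primary endpoint is also reported by component and arm, descriptively.

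Two additions should be avoided. The first is a non-inferiority test on a subset of components at the same 10-point margin. That margin was set against 9% composite failure and is too lenient for rarer events. With an assumed 3 control failures of 103, 8 LIQOSEAL failures would still pass: 0.0485 + 1.645 × 0.0311 = 0.0998. The second is a rule counting a disagreement between PEEP video and case record as a leak. It would alter the primary endpoint one-sidedly in a trial that is already recruiting.

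No treatment criterion changes. The cost is protocol and participant-information wording, one descriptive table, and some scheduling effort at sites where the operating surgeon normally does the follow-up. With recruitment under way, the changes would apply only to assessments not yet made.

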#### Procedure for unblinding if needed {17b}

The surgeon is unblinded after finalization of the primary closure of the dura, to apply the allocated device.

### Data collection and management

#### Plans for assessment and collection of outcomes {18a}

##### Preoperative data

Demographic information (i.e., gender, childbearing potential, age, length, weight, and body mass index), medical and surgical history (i.e., indication for surgery, allergies, tobacco use, medication use), and comorbidity of the patient will be collected. A physical exam is performed during screening. All female patients of child-bearing age will undergo a pregnancy test.

##### Intraoperative data

The device used and its size, LOT number, size of trepanation, any use of autologous material, and type of suture are recorded.

To determine the intraoperative CSF leak before and after the application of the device, the PEEP will be increased to 20 cmH2O for 20 s. First, this test will be performed before closure of the dura to determine safety for the postoperative intracranial field (control of hemorrhage, swelling or other potential adverse effects). Upon completion of the primary sutured dural closure and before the application of the sealant, the closure of the dura will be evaluated for CSF leakage by repeating the test. The patient is excluded if there is no leakage at PEEP of 20 cmH2O for 20 s. Two minutes after application of the device, the test will be performed for a third time to evaluate CSF leakage. All 3 PEEP elevations and application of the device will be recorded on video. A photograph will be taken before and after device application.

After the procedure, end users (surgeons, scrub nurses) will be invited to complete several closed-end questions regarding their user experience with LIQOSEAL.

##### Postoperative data

During the hospitalization, the subject will be monitored daily for clinical signs of infection. The surgical wound will be inspected daily starting 24 h after surgery. Blood analysis and a wound culture will be performed if there are clinical signs of infection. In case of CSF leakage from the incision, a β-2 transferrin test will be performed. Data will be collected every 24 h from 24 h after surgery until discharge or day 7 (whichever comes first).

The clinical data to be collected on the e-CRF includes the following: body temperature.

In case of signs of infection, the following data will be collected as well: C-reactive protein (CRP), leucocytes, and culture of wound.

The signs of infection will be classified to the Centers for Disease Control and Prevention (CDC) standard of Surgical Site Infection (SSI) and recorded in the e-CRF.

All subjects will undergo an MRI on day 90. The MRI will be performed to collect data on the presence and amount of pseudomeningocele (any subcutaneous fluid on T2) as well as the long-term thickness of dura mater and investigational device.

Independent radiologists will analyze the MRIs of all subjects for the outcome measurements. Each MRI will be evaluated by 3 independent radiologists, whereas the analysis then will be based on minimally 2 out of 3 evaluations (whom are in consensus).

Postoperative assessments are not blinded.

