##### Secondary endpoints

*Safety*
Device-related adverse events (AEs) and serious adverse events (SAEs) throughout the study up to 90 days after surgery.Complications requiring surgical re-intervention up to 90 days after surgery.

*Performance*
Any pseudomeningocele as confirmed on magnetic resonance imaging (MRI) at day 90.Volume of pseudomeningocele as determined on MRI at day 90.Ease of use and application of the LIQOSEAL

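### The protocol does not blind the radiologists whose day-90 MRI reading decides a component of the primary endpoint

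*Protocol article*

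**What the plan says.** All in the Protocol article.

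- **Postoperative data:** "Independent radiologists will analyze the MRIs of all subjects for the outcome measurements", and "Each MRI will be evaluated by 3 independent radiologists". The analysis rests on at least two of the three evaluations agreeing. The section then closes with "Postoperative assessments are not blinded".
- **Who will be blinded {17a}:** "The surgeon is blinded for group allocation until finalization of the primary closure of the dura". Nobody else is listed.
- **Primary endpoint:** one of the five components is "Pseudomeningocele >20 cc as confirmed on MRI".
- **Secondary endpoints:** two more outcomes come from the same scan, "Any pseudomeningocele as confirmed on magnetic resonance imaging (MRI) at day 90" and "Volume of pseudomeningocele as determined on MRI at day 90".
- **Postoperative data, again:** the day-90 MRI also serves to record the long-term thickness of the dura and of the investigational device.

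**The concern.** Deciding whether a fluid collection exceeds 20 cc means drawing its border on the image, and near the cut-off that is a matter of judgement. A reader who knows the arm can lean either way without intending to. The surgeon cannot be masked when applying a patch or a hydrogel, but a radiologist reading a scan three months later has no need to know which was used. The article gives no reason for leaving the reading open, and it calls the radiologists independent without saying that this means masked.

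In a non-inferiority trial, a lean towards the investigational arm moves the observed difference away from the margin and makes a false claim of non-inferiority easier. A lean against it costs power. The superiority test that follows a positive non-inferiority result uses the same readings and carries the same exposure.

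**Working it through.** **1. Is any reader masked?** Set side by side, the Postoperative data section describes the three-radiologist reading and then says, without qualification, that postoperative assessments are unblinded. The section on who is blinded lists the surgeon alone. The unblinding section concerns the surgeon alone. No section exempts the radiologists.

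**2. The plan's own sample size.** Inputs from Sample size {14}: success 91% in both arms, margin 10 points, one-sided alpha 5%, power 80%, attrition 10%.

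- n per arm = (1.645 + 0.842)² × 2 × 0.91 × 0.09 / 0.10² = 101.3, so 102
- 102 / 0.9 = 113.3, so 114 per arm and 228 in total

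This reproduces the stated figure, so 102 evaluable patients per arm is the plan's working number.

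**3. Sensitivity to reading bias (the bias is an assumption).** Take the truth at the margin: control success 0.91, investigational success 0.81. Let a net fraction b of investigational patients be counted as successes because of a favourable reading. For the Wald test:

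- SE(b) = √[0.91 × 0.09/102 + (0.81 + b)(0.19 − b)/102]
- P(declare non-inferiority) = Φ(b/SE(b) − 1.645)

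For b = 0.02: SE = √[(0.0819 + 0.1411)/102] = 0.0468, and Φ(0.02/0.0468 − 1.645) = Φ(−1.217) = 11.2%.

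| Net share read favourably, b | Patients of 102 | Type I error, normal approximation | Type I error, exact enumeration of the Wald test |
|---|---|---|---|
| 0 | 0 | 5.0% | 5.5% |
| 1% | about 1 | 7.6% | 8.3% |
| 2% | about 2 | 11.2% | 12.2% |
| 3% | about 3 | 16.0% | 17.2% |
| 5% | about 5 | 30.1% | 31.6% |

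If the lean runs against the investigational arm and both arms truly succeed at 91%, power falls from 80.2% to 70.8, 60.3, 49.5 and 30.1% for the same four values of b.

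**4. Does the two-of-three rule work?** For a yes/no call there are 2³ = 8 patterns of three readings, and every one has at least two readers in agreement. If volumes are measured instead, the median of three exceeds 20 cc exactly when at least two of them do. The rule therefore always gives an answer for the primary component, and likewise for the presence of any pseudomeningocele.

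**The case against.** **The sentence may be about site assessments.** The statement on blinding could be meant for bedside wound checks, and a fuller protocol or imaging charter, not shown, might mask the readers. The article never names the radiologists as unblinded, so the fair wording is that the protocol does not blind them. But this is not a case of detail left to another document. The article makes an unqualified statement directly after describing the MRI reading. If the readers are in fact masked, that statement is wrong and still needs correcting.

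**The size is hypothetical.** This stands. The bias in the table is assumed, runs in one direction, affects one arm and is set at the margin. To change a result, at least two of three readers must err the same way on the same scan, in a patient with no other component of the composite. The documents do not say what share of failures would come from the 20 cc component alone. The triple reading is a real safeguard against one stray reader. It is a weaker one against a lean that several readers share because they know the arm.

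**Masking may be imperfect.** This also stands in part. The documents do not say how visible the patch or the hydrogel is at day 90. That the same radiologists measure device thickness, and would learn the arm from doing so, is a plausible inference and not stated. Nor is it stated that reading takes place off site. Data management {19} mentions only image transfer software.

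**A stronger reading to avoid.** A reader might infer that the agreement rule cannot be met for a measured volume, so that usable scans become non-evaluable and drop out of the mITT set. The documents do not support this. Membership of mITT depends on evaluable primary endpoint data, and the 20 cc call always resolves by majority. How three volumes are combined for the secondary volume endpoint is not stated, but an article may leave that to a fuller document.

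**Conclusion.** The point holds as a matter of blinding. The protocol leaves unmasked the radiologists who decide one primary component and two secondary endpoints, in a trial that is otherwise open once the dura is closed. That rests on the text alone.

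The consequence can be bounded only by assumption. A net 1 to 5% of investigational patients read favourably would take the one-sided type I error from 5% to between about 8 and 30%, with about two patients per arm enough to roughly double it. These figures show how sensitive the comparison is; they do not predict that the bias will occur, and the two-of-three majority makes the larger values less likely. The sample size and the agreement rule are not in question.

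**What to change.** - Give the same three radiologists the scans stripped of allocation, site and clinical data.
- Have the calls on more than 20 cc and on any pseudomeningocele recorded and locked before any measurement of dura or device thickness, if the same readers make that measurement.
- Amend Who will be blinded {17a} to list the MRI readers, and limit the closing sentence of Postoperative data to the assessments that really are open.
- Keep the two-of-three rule for the yes/no calls.

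The cost is some de-identification work and a fixed reading order, with the same readers, scans and sample size. The downside is that masking may be incomplete if the patch can be recognised on the day-90 scan.
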